## b. End Points – Safety

Safety measures:

- Sponsor to deliver bottled water to patient’s home regularly, to avoid any danger to them if they carry heavy loads of water home.
- Hyflux is a public listed water company in Singapore with high quality standards for water products and ELO Water Pte Ltd is a Hyflux Group company. The ELO water has been approved by AVA Singapore for sale in Singapore since November 2015.

# 3. STUDY POPULATION

### 3.1. List the number of subjects to be enrolled.

Total 150 patients: 75 patients in ELO water arm and 75 patients in placebo water arm

### 3.2. Criteria for Recruitment

All patients must fulfil all of the Inclusion criteria (Section 3.3) and do not present with any of the Exclusion criteria (Section 3.4).

### 3.3. Inclusion Criteria

1. 21 years old to 70 years old inclusive
2. Type 2 diabetes mellitus patient
3. HbA1c ranging between 8.0% to 11% inclusive, within the last 6 months

### 3.4. Exclusion Criteria

1. Type 1 diabetes patients
2. Pregnant or lactating women
3. Comorbid conditions requiring fluid intake restriction
4. Patients who are unable to drink water due to inability to swallow or gastrointestinal conditions e.g. stroke or neurological disorders with inability to swallow fluids safely, bedridden patients with high risk of aspiration pneumonia, patients with oesophageal strictures, radical stomach resections or other conditions that makes drinking water unsafe

### 3.5. Withdrawal Criteria

Any patient will be withdrawn from the study if any of the criteria apply:

1. The patient withdraws consent
2. The patient is no longer able to participate , or the investigator, in discussion with the patient’s attending physician(s), decides to terminate participation on medical grounds

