### 6.2. Contraception and Pregnancy Testing

- Pregnant or lactating patients are excluded from the study
- Any patient who becomes pregnant during the study will be withdrawn from the study.
- This exclusion is because pregnant and lactating women have changes in their insulin sensitivity as a result of hormonal change

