###### *b. Study Visits and Procedures*

Refer to Table 1 for the schedule of study review visits.

At each CGH review visit:

- Blood and Urine tests (table 3) will be performed as per scheduled
- Water diary record will be reviewed
- Patients are asked if they have any adverse reactions to the water assigned
- Body weight and height, blood pressure are taken

*c. Final Study Visit:*

- The scheduled final visit should occur after the patient has undergone 24 weeks of treatment or at the early withdrawal
- This visit includes a visit to CGH clinic/ CTRU.
- The week 24 blood tests (see table 3) will be performed at this visit.

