# 9. SAFETY MEASUREMENTS

### 9.1. Safety Evaluation Criteria

Clinical observation and laboratory results will be used to evaluate the wellbeing of the patient on a continual basis throughout the duration of the study.

In the event that the Investigator considers that the wellbeing of an individual patient is unacceptably at risk as a result of participation in the study then the individual patient will be withdrawn from the trial.

In the event that the withdrawal of an individual also has wider implications for the wellbeing of other participating patients, then the study will be suspended and an investigation conducted to determine whether the trial should be continued in the proposed or a modified form or terminated.

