### 11.2. Statistical and Analytical Plans

Categorical data will be presented as frequency (percentage). Continuous data will be presented as mean (SD), unless specified otherwise. The differences in characteristics will be examined using Chi-Square test or Fisher’s Exact test for categorical variables, and 2-sample t-test or Mann Whitney U test for continuous variables. For repeated measures variables, mixed models analysis will be used to account for drop-outs.

A two tailed, p-value of <0.05 was considered statistically significant. Statistical analysis will be performed with SPSS statistical software, version 19.0 (IBM Corp. Armonk, NY).

A statistical analysis for month 3 data is planned in order to study the short term outcomes.

This RCT will be analysed by both intention-to-treat (ITT) and per protocol (PP) approach. Patients’ non-compliance will be monitored via their water diary. The compliance rate will then be adjusted in the data analysis.

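### Patients taken out on medical, safety or pregnancy grounds leave the study and not only the water, so the ITT analysis lacks a true Week 24 HbA1c for some who still consent and could be measured

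*Protocol*

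**What the plan says.** Section 3.5 opens with "Any patient will be withdrawn from the study if any of the criteria apply". Criterion 1 is withdrawal of consent. Criterion 2 covers a patient who can no longer take part and the case where the investigator "decides to terminate participation on medical grounds". Both lead to the same result.

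Two other sections use the same exit. Under 9.1, if the investigator judges that taking part puts the patient's wellbeing unacceptably at risk, "then the individual patient will be withdrawn from the trial". Section 6.2 states: "Any patient who becomes pregnant during the study will be withdrawn from the study".

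Section 6.3, item c, sets the last measurement: "The scheduled final visit should occur after the patient has undergone 24 weeks of treatment or at the early withdrawal", and "The week 24 blood tests (see table 3) will be performed at this visit". Table 3 includes HbA1c, so a patient who leaves early does give an HbA1c sample at exit. No section lets a patient stop the water and remain in follow-up to Week 24.

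The primary endpoint in 2.4 is the HbA1c reduction over 24 weeks. Section 11.2 says: "This RCT will be analysed by both intention-to-treat (ITT) and per protocol (PP) approach". It names a mixed model to deal with drop-outs, and says that non-compliance will be followed through the water diary and adjusted for.

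**The concern.** An ITT analysis asks what happened at Week 24 to everyone randomised, whatever they went on to do with the water. Only withdrawn consent obliges follow-up to end. For exits on medical, safety or pregnancy grounds the protocol ends follow-up by its own rule, although the outcome is a blood test already scheduled at the same single centre.

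The gap is then left to the mixed model. That model is valid if, given the HbA1c values already observed, leaving is unrelated to the values not observed. Exit on medical grounds is where this is least secure. The model's prediction for leavers also rests mainly on patients who stayed on the water, so it does not show what happened after stopping.

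The label in 6.3 item c adds a second risk. A sample taken at, say, Week 9 could be entered as a Week 24 result. A statistical analysis plan can add sensitivity analyses, but it cannot restore a sample that the protocol does not collect.

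**Working it through.** **1. Who is affected, by section**

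| Situation | Rule | HbA1c at exit | HbA1c at Week 24 |
|---|---|---|---|
| Consent withdrawn | 3.5, criterion 1 | Yes, if the patient agrees | No, unavoidable |
| Ended on medical grounds, or no longer able to take part | 3.5, criterion 2 | Yes (6.3 c) | No, by rule |
| Safety | 9.1 | Yes (6.3 c) | No, by rule |
| Pregnancy | 6.2 | Yes (6.3 c) | No, by rule |
| Drinks little or no study water | No withdrawal rule; 11.2 tracks and adjusts | Not applicable | Yes, apparently |

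The point concerns rows 2 to 4.

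**2. The plan's own sample size (11.1)**

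Inputs: d = 0.5, 80% power, 5% level; two-sided from 11.2.

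- Normal approximation: n = 2 × (1.960 + 0.842)² / 0.5² = 62.8, so 63 per arm. The exact t-test gives 63.8, so 64. The stated 65 is reproduced within 2 patients.
- Dropout: 65 × 1.15 = 74.75, so 75 as stated (65 / 0.85 = 76.5, so 77).
- With 15% missing: 75 × 0.85 = 63.75 per arm, t-test power 80.0%.

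The sample size is not in dispute here.

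**3. How many patients**

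150 × 0.15 = 22.5. The 15% covers every kind of dropout, and the protocol gives no breakdown. The number who still consent and could be measured at Week 24 therefore lies between 0 and about 22.

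**4. Possible bias in the arm difference**

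Bias = (missing fraction × shift in the ELO arm) − (missing fraction × shift in the control arm), where the shift is the true Week 24 mean of the missing patients minus the model's prediction. Assumptions: 15% dropout in each arm, and a shift of 0.3 to 1.0 HbA1c points in one arm and none in the other.

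- All dropouts recoverable: 0.15 × 0.3 = 0.045; 0.15 × 1.0 = 0.15.
- One third recoverable (assumption): 0.05 × 0.3 = 0.015; 0.05 × 1.0 = 0.05.
- Similar shift and similar missing fraction in both arms: the two terms cancel, and the bias is near zero.

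**5. Power if Week 24 values are retrieved**

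Measured per arm = 75 × (1 − 0.15 × (1 − f)), where f is the share of dropouts retrieved. If retrieved patients keep no effect, d = 0.5 × 63.75 / measured per arm.

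| f | Measured per arm | Missing in total | Power, full effect kept (d = 0.5) | d, no effect kept | Power, no effect kept |
|---|---|---|---|---|---|
| 0 | 63.75 | 22.5 | 80.0% | 0.500 | 80.0% |
| 25% | 66.6 | 16.9 | 81.7% | 0.479 | 78.3% |
| 50% | 69.4 | 11.3 | 83.3% | 0.459 | 76.6% |
| 75% | 72.2 | 5.6 | 84.7% | 0.442 | 75.0% |
| 100% | 75 | 0 | 86.0% | 0.425 | 73.4% |

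Midway, with full retrieval and half the effect kept, d = 0.5 × (0.85 + 0.15 × 0.5) = 0.4625 and power is 80.3%.

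**The case against.** The best defence is that the plan already copes. It takes an HbA1c at exit, adds it to those at Weeks 0, 6 and 12, and names a mixed model for drop-outs. Sensitivity analyses of missing-at-random belong in the analysis plan, which is not shown. Both arms drink the same volume under blinding, and 9.2 states no known adverse effects, so the documents give no reason to expect medical withdrawals to differ by arm. The number affected may be very small, and retrieving off-water values could lower power.

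Much of this stands. The exit value makes missing-at-random more plausible, equal shifts cancel, and power could fall to about 73%. It does not remove the gap: an exit value is not a Week 24 value, and its label invites treating it as one. Dilution from patients who stopped is part of the ITT effect, so it is no reason to leave them unmeasured.

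A reader might infer three stronger claims, which the documents do not support:

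- *Everyone who stops the water is lost.* Criterion 2 speaks of ability to participate, not of drinking. Following non-compliance by diary and planning both ITT and per-protocol analyses makes sense only if poor drinkers stay in follow-up.
- *The bias is a sizeable fraction of the 0.5-point target.* In 2.4 that figure is a reduction to be achieved, not a difference between arms, and 11.1 sizes the trial on a standardised effect with no SD. It is not a valid denominator.
- *Retrieval leaves power unchanged.* That holds only near the case where about half the effect persists after stopping.

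**Conclusion.** The point holds for exits under 3.5 criterion 2, 9.1 and 6.2. These end follow-up in the same way as withdrawn consent, so the promised ITT analysis has no true Week 24 HbA1c for patients who still consent and could be measured, and it relies on missing-at-random where that is weakest.

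The size is uncertain and may be small. The recoverable number is 0 to about 22 of 150. The bias of 0.045 to 0.15 points is an upper case: it takes every dropout as recoverable, 15% missing in each arm, and an assumed shift in one arm only. One third recoverable brings it to 0.015 to 0.05. The protocol supplies neither the shift nor the recoverable share.

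This is a worthwhile, inexpensive improvement. It does not invalidate the design.

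**What to change.** - In 3.5, 6.2, 6.3 item c and 9.1, define two separate events: stopping study water, and withdrawing consent for follow-up.
- Ask every patient who stops the water but still consents to attend the remaining scheduled visits, at minimum for the Week 24 HbA1c.
- In 6.3 item c, name the early samples as exit samples, record their date, and analyse them at their actual time and not as Week 24.
- In 11.2, state that HbA1c values obtained after stopping are included in the ITT analysis.

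When and why the water is stopped stays as the protocol and the investigator decide; only the collection of data afterwards changes.

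The cost is protocol and consent wording, plus visits and blood tests already in the schedule for at most about 22 patients. The statistical price is the power range shown above for full retrieval, about 73% to 86%, which should be acknowledged when the change is made.

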### 3.6. Subject Replacement

No subject replacement in this study.

# 4. TRIAL SCHEDULE

Table 1 in the following provides a flow chart presenting the study visit schedules and the study activities for the visits.

###### Table 1: Trial schedule

| **Week** | **0** | **6** (+/– 1 week) | **12**  (+/– 1 week) | **24**  (+/– 1 week) |
| --- | --- | --- | --- | --- |
| Consent taking | **X** |  |  |  |
| Inclusion &  Exclusion Criteria  Check | **X** |  |  |  |
| CGH clinic review^a^ | **X** | **X** | **X** | **X** |
| Vital Signs (BP) | **X** | **X** | **X** | **X** |
| Height and Weight | **X** | **X** | **X** | **X** |
| Blood and Urine tests^b^ | **X** | **X** | **X** | **X** |
| Completion of study |  |  |  | **X** |

*a :CGH review will be performed on Week 0, 6, 12, 24 and whenever there is any adverse events. Review will include review of water diary and to ask patient whether there has been any adverse effect, and / or changes in medications, diet and physical activities*

*b: Blood and Urine tests for HbA1c, Haemoglobin, Liver function test (ALT, AST, GGT), Serum creatinine and calculated eGFR, Fasting Lipid profile – Triglyceride, Total Cholesterol, LDL, HDL, Fasting plasma glucose, Plasma Hypoxia inducible factor HIF-1α, Long chain acyl carnitine (C16) and Urine ACR*

# 5. STUDY DESIGN

This is a randomized, controlled, patient and assessor-blind study, with 2 treatment arms in a single centre for 24 weeks. The 2 treatment arms are as shown on Table 2.

###### Table 2: Study arms

| **Treatment arm** | **ELO water** | **Placebo drinking water** |
| --- | --- | --- |
| Drinking 1.5 Litre water daily | ELO bottled water | Normal bottled drinking water |
| Diabetes treatment | Patient’s existing medications | Patient’s existing medications |

A total of 150 Type 2 diabetes mellitus patients who are eligible for the study will be enrolled into this 24 week study.

1. Each patient will be allocated a subject number for the study.
2. Once consented, patients who are recruited will be stratified according to their gender and will be randomised to the either of the 2 treatment arms (see table 2) in the ratio of 1:1.
3. Baseline blood tests (see table 3) will be done at a CGH clinic or CTRU.
4. Patients in both treatment arms will be issued water for drinking that is delivered to their home regularly (Bottled ELO water 1.5 litres or placebo bottled drinking water 1.5 litres) in non-identifying bottles that do not reveal to the patients as to which type of water they are consuming.
5. Study team member will remind patients regularly (via phone call or text message) to drink the study issued water, in order to archive the compliance.
6. Patients are instructed to consume 1.5 litres in divided servings per day. No metal containers or utensils to be in contact with the ELO water. The water cannot be heated or microwaved and should not be mixed with other beverages and consumed.
7. Patients are advised to drink other fluids or water in addition to the 1.5 litres of the bottled water to fulfil their daily water requirements of about 2-3 litres per day.
8. Patients are advised to strictly continue taking their prescribed existing medications and attend scheduled medical appointments throughout the study period.
9. No changes to be made in their diet, physical activity or medications during the study period.
10. Blood tests are performed at week 0, 6,12, and 24 (see table 3)
11. Patients are instructed to keep a water diary

###### Table 3: Laboratory Test at Week 0, 6, 12, 24 weeks

| **Test** | **Collection Tube** | **Volume** |
| --- | --- | --- |
| HbA1c | K^2^EDTA Tube | 2mls |
| Hb |  |  |
| Liver function test (ALT, AST, GGT) | SST Tube with clot activator | 5mls |
| Serum creatinine and calculated eGFR |  |  |
| Fasting Lipid profile – TG, TChol, LDL, HDL |  |  |
| Fasting plasma glucose |  |  |
| Plasma Hypoxia inducible factor HIF-1α | Lithium Heparinised Tube | 8-10mls |
| Long chained acyl carnitine | Lithium Heparinised Tube | 8-10mls |
| Urine ACR | Urine Collection Bottle | At least 10mls |

Special laboratory tests used in the study

1. Plasma HIF-1α

This will be done using an ELISA based test kit from ThermoFischer

Scientific.The Thermo Scientific™ HIF-1 Alpha ELISA Kit measures human hypoxia-inducible factor 1-alpha (HIF1A) protein in plasma using the quantitative sandwich ELISA method. HIF1A standards and samples are captured by a polyclonal HIF1A antibody on the precoated plate and detected using a biotinylated monoclonal HIF1A antibody reactive to epitopes other than the capture antibody. The biotinylated detection antibody is then bound to streptavidin-HRP, which catalyzes the conversion of TMB to a colored derivative. olour development is linear for the assay’s dynamic range and directly proportional to the amount of HIF1A present in the sample.

1. Plasma acyl carnitine assay

The plasma level of acylcarnitines of various carbon lengths will be measured using tandem mass spectrometry.

### 5.1. Summary of Study Design

- The study involves 150 Type 2 diabetic patients with HbA1c between 8% and 11% inclusive.
- 2 study arms – ELO water arm and Placebo drinking water arm  Reviews at CGH according to trial schedule in table 1
- Blood and urine tests are taken at week 0, 6, 12, and 24.

# 6. METHODS AND ASSESSMENTS

- Blood and urine tests
- Review of water diary
- The data will be stored in a study designated hard drive which will be retained for a period of 7 years and be erased after that.

### 6.1. Randomisation and Blinding

Randomization:

Stratified randomization will be performed for this study. Recruited patients will be stratified according to their gender and will be randomly assigned to ELO water arm or Placebo drinking water arm in a 1:1 ratio. A randomisation list will be generated by an independent biostatistician. Blinding of drinking water bottles will then be packaged according to the randomization list. Treatment allocation will be performed by the study nurse once all the recruitment criteria have been fulfilled and consent obtained.

Blinding:

ELO water Pte Ltd (A Hyflux Group Company) will blind the Hyflux factory bottled ELO water and Hyflux factory bottled Placebo drinking water by similar packing and label it as Water A or Water B, to unidentified drinking water bottles for both arms of the study. Water A or Water B for ELO water or Placebo drinking water will be pre-determined by the independent biostatistician.

Water bottles will be delivered to the patient’s home at regular intervals by an independent logistics team (who will not know what is Water A and Water B). A designated CGH staff member will co-ordinate with the logistics team for delivery of the correct type of bottled water to the patients. PI, attending investigators, study team members, and patients will not be able to identify the type of water the patient has been consuming.

### 6.2. Contraception and Pregnancy Testing

- Pregnant or lactating patients are excluded from the study
- Any patient who becomes pregnant during the study will be withdrawn from the study.
- This exclusion is because pregnant and lactating women have changes in their insulin sensitivity as a result of hormonal change

### 6.3. Study Visits and Procedures

###### *a. Screening Visits and Procedures (Week 0)*

Patients will be screened to determine eligibility for participation in the study. The following will be performed and documented at the Week 0 visit:

1. Obtain written informed consent
2. Review of Inclusion/Exclusion criteria
3. Baseline blood tests and urine tests
4. Review patient compliance to his/her existing medications

###### *b. Study Visits and Procedures*

Refer to Table 1 for the schedule of study review visits.

At each CGH review visit:

- Blood and Urine tests (table 3) will be performed as per scheduled
- Water diary record will be reviewed
- Patients are asked if they have any adverse reactions to the water assigned
- Body weight and height, blood pressure are taken

*c. Final Study Visit:*

- The scheduled final visit should occur after the patient has undergone 24 weeks of treatment or at the early withdrawal
- This visit includes a visit to CGH clinic/ CTRU.
- The week 24 blood tests (see table 3) will be performed at this visit.

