### 9.2. Collecting, Recording and Reporting of Serious Adverse Events (SAEs)

A serious adverse event (SAE) is any untoward medical occurrence that:

- Results in death.
- Is life-threatening (immediate risk of death)
- Requires inpatient hospitalization or prolongation of existing hospitalization.
- Results in persistent or significant disability/incapacity.
- Results in congenital anomaly/birth defect.
- Is a Medically important event.

All SAE will be collected, documented, assessed and reported by the PI to SHS CIRB according to its guideline, and to the Sponsor in the prescribed SAE form.

There are no known adverse effects of drinking the ELO water.

Complaints will be recorded in the case notes, and possible adverse events will be recorded in a separate section in the case records form (see attached).

PI and co-investigators will determine the severity, causality and expectedness of adverse events. If the investigator determines that the event may jeopardize the subject and/or may require intervention to prevent one of the other adverse event outcomes, the important medical event will be reported as serious. Causality will be defined as related/not related, and expectedness will be based on reported adverse events in the summary of product of characteristics.

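### The visit question in section 6.3.b asks about reactions to the water, so patients judge cause before the investigators do; it should be one cause-neutral question, aligned with Table 1 footnote a and section 9.2

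*Protocol*

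**What the plan says.** Three parts of the protocol govern how adverse events come to light.

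- **Section 6.3.b (Study Visits and Procedures)** lists what is done at each review visit. Its safety item reads "Patients are asked if they have any adverse reactions to the water assigned".
- **Table 1, footnote a** describes the same reviews. Staff are "to ask patient whether there has been any adverse effect, and / or changes in medications, diet and physical activities". On timing it says "CGH review will be performed on Week 0, 6, 12, 24 and whenever there is any adverse events".
- **Section 9.2** opens its definition with "A serious adverse event (SAE) is any untoward medical occurrence that" and then lists the seriousness criteria, none of which depends on cause. On collection it says "All SAE will be collected, documented, assessed and reported by the PI to SHS CIRB according to its guideline". On recording it says "Complaints will be recorded in the case notes, and possible adverse events will be recorded in a separate section in the case records form". It gives severity, causality and expectedness to the principal investigator and co-investigators, with causality in two classes, related and not related. It also states the starting position: "There are no known adverse effects of drinking the ELO water".

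Section 9.1 adds clinical observation and laboratory results as safety sources, and section 8.6 has all medications documented.

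**The concern.** Asking about reactions to a named product invites the patient to filter by cause. Few people would connect a fall, a hypoglycaemic episode, a chest infection or a hospital stay with bottled water, and they could truthfully answer no. The not-related class in section 9.2 exists to hold such events, but an investigator can classify only what has been reported.

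The stake is the completeness of the safety record. The protocol has no data safety monitoring board (section 9.3), and its safety end-point section lists home delivery and product quality rather than a patient outcome. What patients are asked at visits therefore carries a good part of the safety information. A short list of reported reactions, obtained with this question, would be weak support for the statement that the water has no known adverse effects. The wording has to be settled before follow-up, because events not elicited at a visit cannot be fully recovered afterwards.

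**Working it through.** The protocol states no adverse-event rate, no proportion of events that patients would attribute to the water, and no safety sample-size figure. There is nothing to recompute, so the check compares the passages.

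**Step 1. Who judges cause?** In section 6.3.b the patient does, because the question concerns reactions to the assigned water. In section 9.2 the investigators do. An event that the patient screens out at the first stage does not reach the second by this route. The two sections are inconsistent on this point.

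**Step 2. Does footnote a remove the inconsistency?** In part. It applies to the same visits and is not restricted to the water. Its question about medication changes should also surface events that led to a change of treatment. But the word effect leans towards cause, and section 9.2 uses the same term causally when it speaks of effects of drinking the water. So two sections give different questions for one visit, and neither clearly asks about any new illness or admission whatever its cause.

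**Step 3. What do the other channels catch?**

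- *Collection of all serious adverse events (9.2).* This is an obligation with no attribution filter. The protocol does not name the question or records check by which the team would learn of an admission.
- *Unscheduled review (footnote a).* It takes place when there is an adverse event, so someone must already know of the event.
- *Laboratory tests, weight and blood pressure.* These are taken at Weeks 0, 6, 12 and 24 whatever the patient believes. They would show a sustained change, but not reliably an episode that came and went between visits.
- *Medication record (8.6) and the medication question (footnote a).* These point to events that changed treatment, and not to others.
- *Complaints and possible adverse events (9.2).* Both are written down once voiced.

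**Step 4. How long could a report be delayed?** The intervals between scheduled visits are 6 − 0 = 6, 12 − 6 = 6 and 24 − 12 = 12 weeks. With the one-week windows, the last can reach 25 − 11 = 14 weeks. An event that the patient does not volunteer soon after Week 12 may wait that long for the next scheduled enquiry, and that enquiry is then put in terms of the water.

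**Result.** The inconsistency between 6.3.b, footnote a and 9.2 is real. Its direction is towards under-reporting of events that patients do not attribute to the water. Its size cannot be derived from the protocol.

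**The case against.** The strongest reply is that section 6.3.b is not the only route. It refers to Table 1 for the visit schedule, and footnote a to that table has staff ask more broadly. Serious events are collected regardless of cause, laboratory and clinical measures do not depend on what the patient blames, and a related/not-related classification presupposes that unrelated events are recorded. The case record form is mentioned as attached but is not available here, and its prompt may already be neutral. This reply stands as a limit on the point: some events will be caught by other means. It does not remove the conflict in wording, because site staff working from 6.3.b would ask the narrower question.

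A reader might infer four stronger things that the protocol does not support.

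- *That patients are asked only about the water, so other events go unrecorded.* Footnote a and the channels in Step 3 contradict this.
- *That 6.3.b contradicts the definition in 9.2.* That definition is of serious adverse events, and 6.3.b neither changes it nor limits their collection. The conflict is with who assigns causality and with how the duty to collect all serious events would be met.
- *That complaints are diverted to the case notes and so lost.* The word possible sets a low threshold for the case record form, and the sentence can be read as covering both.
- *That the comparison of arms is biased or uninformative.* The question is the same in both arms, patients and reviewing staff are blinded (section 8.5), and section 11.2 specifies no between-arm safety analysis. Bias would need patients to guess their arm and to attribute events differently according to the guess, and nothing in the protocol shows either.

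**Conclusion.** The point holds as an inconsistency in how adverse events are elicited, with a likely loss of sensitivity. Section 6.3.b makes the patient judge cause first, footnote a is broader but loosely worded, and section 9.2 leaves cause to the investigators. Events that patients do not link to the water may be missed or learned of late.

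The loss cannot be quantified: any figure would need event rates and attribution proportions that the protocol does not give. The conclusion assumes that staff follow 6.3.b as written and that the case record form has no neutral prompt of its own. If the form does have one, the point reduces to aligning the text. The change should still be made, since it is cheap and the missing information cannot be fully recovered once visits have passed.

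**What to change.** Put the same question in section 6.3.b and in Table 1 footnote a: has the patient had any new or worsening symptom, illness, emergency visit or hospital admission since the last contact, whether or not they think it is related to the water? Keep the footnote's separate question on medications, diet and physical activity. Record every positive answer in the adverse-event section of the case record form, check that the form's prompt matches, and leave relatedness to the investigators as section 9.2 already provides.

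The reminder contacts in section 5 should not be counted on to cover the gap after Week 12. They may be text messages, and their frequency is not stated.

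The cost is two lines of protocol text, a matching prompt on the form, and more minor unrelated events for staff to log and classify.
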